## Abstract

**Background:**

Implementation of clinical practice guidelines into daily care is hampered by a variety of barriers related to professional knowledge and collaboration in teams and organizations. To improve guideline concordance by changing the clinical decision-making behavior of professionals, computerized decision support (CDS) has been shown to be one of the most effective instruments. However, to address barriers at the organizational level, additional interventions are needed. Continuous monitoring and systematic improvement of quality are increasingly used to achieve change at this level in complex health care systems. The study aims to assess the effectiveness of a web-based quality improvement (QI) system with indicator-based performance feedback and educational outreach visits to overcome organizational barriers for guideline concordance in multidisciplinary teams in the field of cardiac rehabilitation (CR).

**Methods:**

A multicenter cluster-randomized trial with a balanced incomplete block design will be conducted in 18 Dutch CR clinics using an electronic patient record with CDS at the point of care. The intervention consists of (i) periodic performance feedback on quality indicators for CR and (ii) educational outreach visits to support local multidisciplinary QI teams focussing on systematically improving the care they provide. The intervention is supported by a web-based system which provides an overview of the feedback and facilitates development and monitoring of local QI plans. The primary outcome will be concordance to national CR guidelines with respect to the CR needs assessment and therapy indication procedure. Secondary outcomes are changes in performance of CR clinics as measured by structure, process and outcome indicators, and changes in practice variation on these indicators. We will also conduct a qualitative process evaluation (concept-mapping methodology) to assess experiences from participating CR clinics and to gain insight into factors which influence the implementation of the intervention.

**Discussion:**

To our knowledge, this will be the first study to evaluate the effect of providing performance feedback with a web-based system that incorporates underlying QI concepts. The results may contribute to improving CR in the Netherlands, increasing knowledge on facilitators of guideline implementation in multidisciplinary health care teams and identifying success factors of multifaceted feedback interventions.

**Trial registration:**

NTR3251.

## Background

Concordance to clinical practice guidelines can improve patient outcomes, reduce practice variation, and reduce costs of health care [1-3]. However, implementation of guidelines into daily care is hindered by a variety of barriers related to decision-making behavior of health care professionals and collaboration in teams and organizations [4]. An electronic patient record (EPR) information system with computerized decision support (CDS) functionalities was previously developed to stimulate guideline implementation in cardiac rehabilitation (CR) in the Netherlands [5,6]. Although the CDS system was effective in improving concordance with the guidelines recommendations, there remained a considerable non-concordance due to organizational constraints (e.g., lack of time or resources) [7]. Therefore, we hypothesize that guideline implementation with CDS systems directed at professionals may be more powerful if used in conjunction with other interventions directed at the decision-making processes at the organizational level [8]. This paper describes the design of an evaluation study of a multifaceted intervention combining indicator-based performance feedback and educational outreach visits to improve guideline implementation in a context of multidisciplinary CR teams working with an EPR with CDS already.

### The problem: persisting external barriers to guideline implementation

Poor concordance to clinical practice guidelines is due to various barriers that professionals may face when they try to incorporate practice guidelines into daily care. An often-used classification of those barriers is the division into internal and external barriers [9]. Internal barriers relate to professional knowledge of, and attitudes towards, the guidelines. For instance, professionals may not be familiar with the details of a guideline or may disagree with its recommendations. However, because health care professionals often work within complex organizations, appropriate knowledge and attitudes of professionals are necessary but not sufficient to implement guidelines. Professionals may also encounter external barriers which hamper their ability to execute guideline recommendations. These barriers concern environmental factors related to the organization or health system professional work in, such as a lack of resources. External barriers also include barriers related to patients (e.g., patients may refuse therapies) and to the guidelines themselves (e.g., ambiguities, omissions, and contradictions).

Of the different implementation strategies to overcome barriers to guideline implementation (e.g., education, outreach visits, CDS, and reminders [10]), those providing patient-specific recommendations at the time and place where professionals make clinical decisions are most likely to be effective [2]. A recent systematic review and meta-analysis demonstrated that, in general, CDS increases the chance that recommended therapies are actually prescribed by 57% (odds ratio 1.57; 95% confidence interval 1.35 to 1.82) [11]. In individual trials, however, CDS is not always effective. A systematic review in the area of chronic disease management (including CR) shows that CDS led to significant improvements in the process of care in only 25 out 48 trials (52%) [12]. Attempts to identify critical success factors for CDS systems have provided inconsistent results, and it seems likely that these factors are highly dependent on the time and context of the intervention [13]. Overall, this seems to suggest that CDS is an effective instrument to overcoming internal barriers (i.e., related to clinical decision-making of professionals) to guideline implementation. However, external barriers are probably not addressed by CDS interventions.

This phenomenon that barriers faced by front-line professionals do not reach their managers and policy makers was also described by Tucker and Edmondson [14]. Clinicians may not be familiar with underlying concepts to address external barriers [15] and often lack time to be actively involved in activities other than patient care. This makes successfully overcoming external barriers a challenging endeavor. Therefore, we hypothesize that besides CDS, additional interventions are needed to also address external barriers related to decision-making processes at the organizational level of the health care clinic professional work in.

### Solving the problem: overcoming external barriers by providing a quality improvement intervention with performance feedback and outreach visits

A common approach to changing complex organizations is systematic quality improvement (QI), which focuses on improving an organization’s underlying processes. It relies on data from health care professionals’ own setting and encourages working in multidisciplinary QI teams. The teams’ performance should guide them in improving their practice by the plan-do-study-act (PDSA) cycle, a part of the Model for Improvement [16] (see Figure 1). Performance feedback is a crucial element within the plan and the study step in the PDSA cycle. Quality indicators—i.e., quantitative measures to monitor and evaluate the quality of health care processes that affect patient outcomes [17]—commonly serve as a basis for the feedback. The assumption is that it prompts professionals to change their behavior if they see that their practice does not meet benchmark values (e.g., national target values or average performance within a peer group). A recent Cochrane review on the effect of audit and feedback reported a median absolute increase in compliance with desired practice of +4.3% (interquartile range (IQR) 0.5% to 16%) on dichotomous measures (e.g., proportion of patients adhering to their therapy plan) and +1.3% (IQR 1.3% to 28.9%) on continuous measures (e.g., time between referral and intake). The reviewers suggested audit and feedback to be most effective if provided by a supervisor or colleague, more than once, both verbally and in writing, if baseline performance is low, and if it includes explicit targets and an action plan. Furthermore, the effect of indicator-based performance feedback is likely to be stronger when it is combined with educational meetings, directed towards actively involving care professionals in the improvement process [17].

**Figure 1 Fig1:**
[figure not shown]
**The model for improvement [**
16
**].**

Based on the literature on feedback, we hypothesize that complementing CDS with a performance feedback and outreach visit intervention might be an effective way to involve front-line professionals and their managers together in overcoming external barriers to improve their practice. This matches the conclusion of a substantial proportion (although not all) of systematic reviews concerning the effectiveness of different guideline-implementation interventions [10,18-21]. They indicate that effective strategies often have multiple components and that the use of single-component strategies is less effective [21]. Change is possible, but generally requires comprehensive approaches at different levels (doctor, team practice, hospital, wider environment), tailored to specific settings and target groups [20].

### Aim and objective

Given the positive effect of CDS on decision-making behavior of health care professionals but the remaining practice variation caused by organizational barriers, the development and assessment of an intervention tailored to external barriers to change are necessary. This study aims to intervene on factors influencing the implementation of guidelines at the organizational level in a setting where an existing CDS is used to guide professional decisions. We hypothesize that a web-based QI system with indicator-based performance feedback and educational outreach visits to multidisciplinary care teams will overcome the organizational constraints for changes needed to improve guideline concordance [22]. Table 1 describes the motivation of the elements included in the developed multifaceted intervention based on both the literature and from earlier studies performed in the field of CR by our research group.

**Table 1 Tab1:** **Previous studies—improving guideline concordance in the field of CR**

**Study**	**Description of the studies**
I. *Tackling internal barriers: CDS*	To stimulate the implementation of the Dutch CR Guidelines, an EPR with CDS functionalities named CARDSS (cardiac rehabilitation decision support system) was previously developed [5]. After entering patient data, CARDSS provides its users with a patient-specific, guideline-based rehabilitation program, consisting of recommended rehabilitation goals and therapies. The effect of the system was evaluated in a cluster-randomized trial in 21 CR clinics, which showed that the system increased concordance to the CR guideline: CR professionals using the system better adapted the CR therapy to patients’ needs [7]. Data from the same trial however pointed out that there remained to exist a large variation in CR practice across clinics. For instance, the percentage of patients participating in exercise training varied from 41% in one clinic to 100% in another and the percentage of patients participating in education and counseling programs varied from 39% to 96%.
II. *Persisting barriers after introduction of CDS*	After the trial a qualitative study was conducted to investigate which barriers were reduced and which barriers persisted after introduction of the CDS system [8]. Results from semi-structured interviews with 29 CR professionals showed that the system succeeded in overcoming professional knowledge barriers. For instance, professionals were more aware of the need to use objective instruments to assess patients’ needs and of the therapy decision rules as described in the guidelines. However, two remaining barriers for guideline concordance frequently mentioned were organizational and guideline-related barriers; both can be classified as external barriers according to Cabana et al. [9].
III. *Tackling external guideline-related barriers: revision of the guidelines*	To overcome guideline-related barriers, the clinical algorithm for assessing patient needs in CR was revised [23]. We combined patient data collected by CARDSS and input from academic and practical experts. Assessment of patient needs based on clinical judgment was found to be a source of practice variation and was therefore avoided in the revised algorithm by adding several standardized assessment instruments.
IV. *Tackling external organization-related barriers: pilot study with feedback*	To address the remaining organizational-related barriers, a once-only benchmark-feedback loop was introduced in a pilot study in 21 clinics [22]. Data from the CDS system at different clinics were collected, stored in a central data registry, and used to generate paper feedback reports with benchmark information for each of the clinics. The reports aimed to steer discussions in team meetings, encouraging them to formulate QI plans. Although the reports were positively received by the clinics, many were unable to create time to discuss and actually act upon the report.
V. *Developing quality indicators*	For providing quality feedback to CR clinics, we developed a national preliminary set of quality indicators. This was performed in close collaboration with an expert (representatives from all disciplines involved in CR) and patient panel using a modified Rand method [24]. Within this method, results from both panels were combined with results from a literature search and guideline review in an extensive rating and consensus procedure. Table 3 shows the final set including 18 quality indicators regarding guideline concordance (e.g., complete data collection during needs assessment) and other quality aspects perceived relevant by both panels (e.g., patients participate in satisfaction research). Based on user experiences during this trial, we aim to select a subset of quality indicators to be rolled out on a national level.

**Table 3 Tab2:** **Quality indicator set for cardiac rehabilitation per study arm**

**Study arm**	**Nr**	**Type**	**Quality indicator**
A	1	Structure	Specialized education for patients with chronic heart failure
	2a	Process	Complete data collection during needs assessment for rehabilitation (concerning psychological and social functioning, and lifestyle factors)
(Patient education, quality of life, and lifestyle change therapy [ex. physical activity])			
	3	Process	Patients receive a discharge letter to stimulate continuation of lifestyle changes at home
	4	Outcome	Patients quit smoking
	5	Outcome	Patients improved their quality of life during rehabilitation
B	2b	Process	Complete data collection during needs assessment for rehabilitation (concerning physical functioning and, cardiovascular risk factors)
(Exercise training and physical activity, relaxation and stress management, cardiovascular risk factors, and work resumption)			
	6	Process	Cardiovascular risk factors are evaluated after rehabilitation
	7	Outcome	Patients improve their exercise capacity during rehabilitation
	8	Outcome	Patients meet the physical activity norms
	9	Outcome	Amount of time needed to start resumption of work
A and B	10	Structure	Rehab professionals work with a multidisciplinary patient record
	11	Structure	Long-term patient outcomes are assessed
	12	Structure	Patients participate in patient satisfaction research
	13	Structure	Clinics perform internal evaluations and quality improvement
	14	Process	Average time between hospital discharge and start of rehabilitation
	15	Process	Patients are offered a rehabilitation program tailored to their needs
	16	Process	Patients finish their rehabilitation program
	17	Process	Rehabilitation goals are evaluated afterwards
	18	Process	Cardiologists receive a report after the rehabilitation

The key objective of the study is to assess the effectiveness of a web-based QI system with periodic performance feedback on quality indicators for CR and educational outreach visits to multidisciplinary QI teams to overcome organizational barriers for guideline concordance in the field of CR in the Netherlands. Primary outcome will be the impact of our intervention on concordance to the national CR guidelines (concerning CR needs assessment and therapy indication procedure). Secondary outcomes are changes in performance of CR clinics measured by changes in structure, process, and outcome indicators for CR and changes in practice variation on these indicators. A qualitative process evaluation (concept-mapping methodology) will be used to assess experiences from participating CR clinics and to gain insight into factors which influence implementation of the intervention. The results of this study can be used by those involved in QI of the CR care in the Netherlands. More in general, our study results may contribute to a better understanding of factors that influence the implementation of practice guidelines and can be used to set up multifaceted guideline implementation programs in other fields of health care.

## Methods

### Study design

The effect of the intervention will be evaluated in a multicenter cluster-randomized study with a balanced (2 × 2) incomplete block design. Cluster-randomization is chosen to avoid contamination among professionals within the same clinic [25]. During the trial, clinics will be divided into two study arms (A and B). Using the multidisciplinary character of CR treatment, each arm will receive the intervention (a web-based QI system with feedback and educational outreach visits) directed at one out of the two domains described in the CR guidelines [26]. Clinics allocated in arm A will receive the intervention directed at improving guideline concordance for the psychosocial domain, clinics in arm B for the physical domain (see Figure 2 for an overview of the study flow). In this way, both study arms will serve as each other’s control. For all participating clinics, the study period is 1 year.

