#### Inclusion criteria (patient level)

All consecutive CR patients that undergo the needs assessment procedure in one of the participating clinics will be included in the study. Clinics that participate in the study agree to enter all data of these patients in their EPR.

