### Outcome measures

As in most guideline implementation studies, the proposed intervention is targeted at health care providers and is therefore expected to have a direct effect on process outcomes and to have only indirect, long-term effects on patient outcomes. The primary outcome measure will therefore be concordance, at patient level, to national CR guidelines with respect to the needs assessment (concordance of clinical decisions with the guidelines, for four group-based therapies). We will measure whether patients are treated according to the recommendations of the guidelines (i.e., treating patients who should have been treated and not treating patients who should have been untreated).

Secondary outcome measures are changes in performance of participating clinics as measured by 18 quality indicators for CR (see Table 3) and changes in practice variation on these indicators. Table 1 describes how the indicator set was developed [24].

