### Data collection and validation

During the trial, participating CR clinics will use one of the two available commercial EPR systems with CDS. Each month, participating clinics are requested to extract data from their EPR, and submit it to the CARDSS Online system. After submission, the data are checked for validity and imported to the CARDSS Online database.

To measure data quality and completeness, a data audit will be conducted in each participating clinic at the end of the trial. To do so, we will ask access to an independent, local data source (preferably a digital agenda listing appointments for all therapies offered to CR patients). First, we will use this data source to check if our registration of therapies is correct, i.e., whether these therapies were indeed attended by the patient. To this end, 20 patients randomly selected from our database will be looked up in the independent data source. Second, we will use this source to check if our database is complete, i.e., whether all data of CR patients treated at the clinic also exist in our database (no missing patients). Therefore, 20 patients randomly selected from the independent source will be looked up in our database.

When no independent data source is available, we will ask the clinic in question to interview ten randomly selected patients over the telephone about the therapies they have followed and to check if their answers match our database. Thereafter, we will ask the clinics if we can interview ten randomly selected patients during a therapy session to see if their data is present in our database and if the therapy programs match.

If two or more of the selected patients from the independent source cannot be found in our database or if discrepancies in therapeutic data exist in more than five records, we will consider all the data of the clinic in question to be unreliable and exclude that clinic from the analyses.

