### Statistical analysis

For the primary outcome measures, we will use mixed-effect logistic regression analysis [7,58], including clinic as random effect, to assess the effect of the intervention. Included covariates will be study arm, time since study start, and time × arm interaction. We will focus on the interaction term to assess the difference in change over the study period between the two arms—that is, the effect of the intervention—because we expect concordance to improve gradually.

For the secondary outcome measures, a similar analysis will be conducted, though replacing the logistic function by another link function as appropriate. Changes in practice variation will be assessed by including a random coefficient for ‘time since study start’ in the regression model and comparing the variation in estimated quality scores before and after the study.

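### Indicator 9, time to work resumption, is a censored duration, but the plan gives it the common mixed regression with only the link function changed

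*Protocol article*

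**What the plan says.** Four places in the protocol article bear on this point.

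- **Entry and time frame.** Study design: "For all participating clinics, the study period is 1 year". The section Inclusion criteria (patient level) adds this rule: "All consecutive CR patients that undergo the needs assessment procedure in one of the participating clinics will be included in the study". Entry is therefore continuous, and patients start at different distances from the end of the study period.
- **The outcome.** Outcome measures: "Secondary outcome measures are changes in performance of participating clinics as measured by 18 quality indicators for CR". Indicator 9 in Table 3 is "Amount of time needed to start resumption of work". It is listed under arm B only, so arm A is its control.
- **The analysis.** The Statistical analysis section models the primary outcome by mixed-effects logistic regression with a random clinic effect, arm, time since study start and their interaction. It focuses on the interaction because improvement is expected to be gradual. The secondary outcomes get the same analysis, "though replacing the logistic function by another link function as appropriate".
- **Data flow.** Data collection and validation: "Each month, participating clinics are requested to extract data from their EPR, and submit it to the CARDSS Online system". In the same section, "a data audit will be conducted in each participating clinic at the end of the trial". No date of last extraction is given.

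**The concern.** A link function relates the mean of an observed response to the covariates. A patient who has not resumed work at the last extraction has no observed duration, only the knowledge that it exceeds the time followed so far. No choice of link supplies the missing part. In practice a regression on durations would use the patients who have resumed.

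That selection depends on entry date. An early entrant has many months in which a slow resumption can be seen; a late entrant is seen only if resumption is quick. The observed durations therefore shorten through the year without any change in care. The plan looks for the effect in the change over time and expects it to grow, so the patients who should carry most of it are those whose durations are cut shortest. At stake is the ability to detect an effect on indicator 9, and the credibility of any within-arm trend reported for it.

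**Working it through.** The article gives no figure for indicator 9, so there is nothing of its own to reproduce. It gives neither the distribution of times to resumption nor the programme length; both are assumed below. The clock is taken to start at entry.

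**1. Compression of a difference between groups.** For an exponential time T with mean μ, seen only if it falls within follow-up c:

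E[T | T < c] = μ − c·exp(−c/μ) / (1 − exp(−c/μ))

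Assume means of 3 months (control) and 2 months (intervention), a true difference of 1.0 month.

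| Follow-up c | Control, μ = 3 | Intervention, μ = 2 | Apparent difference |
|---|---|---|---|
| 12 months | 3 − 12(0.0183)/0.9817 = 2.78 | 2 − 12(0.0025)/0.9975 = 1.97 | 0.81 |
| 3 months | 3 − 3(0.3679)/0.6321 = 1.25 | 2 − 3(0.2231)/0.7769 = 1.14 | 0.12 |

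Control patients seem to improve from 2.78 to 1.25 months with no real change. The true difference of 1.0 month shrinks to 0.12 among those with 3 months of follow-up.

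**2. Effect on the planned contrast.** A simulation used uniform entry over 52 weeks, exponential times, resumptions counted only if they occur by week 52, and a straight-line fit of duration on entry time. First there was no effect; then the arm B mean fell linearly to 30% below control by week 52, so the true interaction is −0.3 × mean.

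| Assumed mean (weeks) | Resumption seen | Mean among those seen | Same, last-quarter entrants | False trend in each arm, weeks per year | True interaction | Interaction among resumers |
|---|---|---|---|---|---|---|
| 6 | 88% | 5.2 | 3.0 | −3.6 | −1.8 | −0.4 |
| 10 | 81% | 7.7 | 3.5 | −7.5 | −3.0 | −0.3 |
| 16 | 70% | 10.2 | 3.8 | −12.2 | −4.8 | −0.2 |

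With no true effect the interaction among resumers was about 0 in all three cases: the false trend is common to both arms and cancels. With a true effect, between about a fifth and less than a twentieth of it remains.

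**3. Conditional point on the other indicators.** By their wording in Table 3, indicators 3, 5, 6, 7, 16, 17 and 18 need the end of rehabilitation or an evaluation after it. If extraction stopped at month 12 and programmes lasted L months, the share of entrants without a value would be L/12: 2/12 = 17%, 3/12 = 25%, 4/12 = 33%. Of the 350 patients per clinic assumed under Sample size, that is about 58, 88 and 117. In a patient-level approximation with time counted from entry, the variance of a slope over entry time grows by (1 − L/12)⁻³ = 1.73, 2.37 and 3.38. If extraction continues until the last entrant has finished, the loss is 0%.

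**The case against.** The strongest reply is that the article states no data cut. The 1-year period may describe delivery of the intervention, the sentence on monthly extraction has no end date, and the study-flow figure is not shown. Follow-up windows and denominators are commonly left to the full protocol or analysis plan. This stands, and it is why the point on the seven indicators is conditional.

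It can also be said that a link chosen as appropriate does not commit the sponsor to analysing resumers only. One link could even serve: a complementary log-log link on patient-by-month records is a discrete-time survival model. But that needs the outcome redefined as a monthly yes/no with censored patients kept at risk, which is more than a change of link. For indicator 9 the article does state a method, and as stated it does not deal with unresolved resumptions.

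Three stronger readings are tempting and not supported:

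- **That late entrants are in fact truncated on ten indicators (3–9 and 16–18).** No cut is stated. Table 3 does not say when indicators 4 and 8 are measured, and indicator 9 can end before or during rehabilitation.
- **That a false arm effect would arise.** Equal truncation gives a shared trend that cancels in the interaction; what remains is attenuation.
- **That every indicator should be timed by needs-assessment date.** Discharge letters, goal evaluations and reports to cardiologists are clinic actions at programme end. The article does not say which date its time variable uses, and timing these by entry would credit them with less exposure than they had.

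**Conclusion.** The point holds for indicator 9. The planned regression with another link does not accommodate patients who have not resumed work. If resumers alone are analysed, the interaction is attenuated and both arms show a false improvement. How severe this is depends on the assumed distribution and on how long late entrants are followed: with 12 months of follow-up for everyone the example still loses some of the difference (0.81 against 1.0), and with 3 months nearly all of it (0.12).

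The loss on the seven end-of-rehabilitation indicators, about 17–33% of entrants, is an assumption resting on a month-12 cut and a 2- to 4-month programme, neither of which is in the article.

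Only secondary outcomes are touched. The primary outcome, "concordance of clinical decisions with the guidelines, for four group-based therapies", is not affected.

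**What to change.** **Indicator 9.** Take it out of the common regression and analyse it as a right-censored time-to-event outcome in patients with work to resume. Examples are a Cox or Weibull model with a clinic frailty, arm, calendar time at entry and their interaction. Define the start of the clock, and censor patients who have not resumed at their last extraction. A discrete-time version with a complementary log-log link on patient-month records would keep the planned mixed-model framework. This is a change of wording and code.

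**Extraction.** State the date of last extraction. If it would fall at the end of the 1-year period, keep the inclusion window and continue monthly extraction for patients already included over a fixed window, long enough for the programme and its evaluation. State for each indicator which date places it on the time axis; this need not be the same date for all.

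**Cost.** A few more monthly extractions from records already in use and a later database lock, with no extra patients or visits. If the full protocol already extends follow-up, only the model for indicator 9 needs changing.
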